- (3) Psychoeducation: Carers will select at least 20 out of 30 learning units from the that are relevant to them from the online iSupport program or a hardcopy of iSupport handbook to learn over the first 6 months of the trial and revisit or learn new units when they feel it is needed in the second 6 months. The expected time spent on their engagement with the online iSupport learning units will be no more than 12 hours in total. The completion of each unit will be measured through the program design and will be recorded as data for compliance with the intervention. Carers will receive a certificate for each unit they complete, a strategy to motivate them in the program.
- (4) Carer support group: In each study site, the facilitator will assign the 23 carers into one of two support groups. The facilitator will conduct a monthly online carer support group meeting lasting no more than 30 minutes. Managing transitions between care settings and types and managing disease progression will be standard meeting agenda so that carers can share their experiences and support each other in these dementia caregiving areas. The meetings will be recorded for carers in the same group to access. The facilitator will also create carer support groups in WhatsApp to encourage carers to talk or send text messages to their peers in the same group to strengthen social support. Facilitator will communicate with participants via phone calls if they have no access to zoom or WhatsApp. The facilitator will analyse group interactions, investigate carers' needs for support and provide feedback to them.
- (5) Feedback on services: The facilitators will collect carers' feedback via regular carer support group meetings, and discuss the feedback in their organisation's quality improvement meetings.
- (6) Confidentiality: Carers will follow an agreed protocol to maintain confidentiality and privacy in group activities.
- (7) Carers will undertake an online survey at three time points: baseline, 6 months, and 12 months. Each survey will take about 30 minutes. Carers will also undertake a monthly 10-minute survey (online or hardcopy) to document the previous month health care services utilisation. They will be notified about each survey by email and an SMS message sent by the researcher. Carer can reply 'stop' to indicate the termination of the reminder and withdrawing from the study. Therefore, the time commitment for this group of carers would be no more than 27 hours.

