**Who will be confirming or renegotiating consent with participants and what process will be undertaken?**

**(1) SALHN and Resthaven SA sites:**

The researcher, [name] who obtained consent form from participants will be confirming or renegotiating consent with participants. She will send SMS to participants to remind them of each follow-up survey. She will also remind participants that they have the right to withdraw at any stage of the study. Participants can reply 'stop' to indicate the termination of the reminder and withdrawing from the study.

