**What impact will a participant withdrawing have on the data and how will this be responded to?**

We have assumed an attrition rate of 40% in sample size calculation. This sample size will ensure a participant withdrawing has little impact on the data and statistical power. A clear flow form about the numbers of participants' recruitment, allocation, withdraw, and analysis will be reported in the project reports and publications to foster transparency of the study.

A withdraw consent form will be used if participants wish to withdraw during the research. Participants will be informed that data collected up to the time of withdraw will be used unless they suggest otherwise.

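### A 'stop' reply to a survey text both ends reminders and withdraws the carer, with no reminder-only option, so 12-month primary outcomes can be lost needlessly

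*Protocol*

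**What the plan says.** Under Participant commitment, in both the Arm 1 text and Arm 2 item (7), the protocol treats a carer's 'stop' reply as a way "to indicate the termination of the reminder and withdrawing from the study". The same rule is item (2) of the answer on confirming or renegotiating consent. It recurs for each group of sites under the question of who will confirm consent: "Participants can reply 'stop' to indicate the termination of the reminder and withdrawing from the study".

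The surveys that prompt such a reply are of two kinds. Arm 2 item (7) says "Carers will undertake an online survey at three time points: baseline, 6 months, and 12 months" and then "Carers will also undertake a monthly 10-minute survey (online or hardcopy) to document the previous month health care services utilisation". On notification it says "They will be notified about each survey by email and an SMS message sent by the researcher".

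A second withdrawal route exists. The section on the impact of a participant withdrawing says "A withdraw consent form will be used if participants wish to withdraw during the research", and item (4) of the renegotiation answer also provides for this form (Appendix H), where appropriate. The same impact section says "data collected up to the time of withdraw will be used unless they suggest otherwise".

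The primary hypotheses are set at 12 months (Hypothesis section). Attrition of 40% is assumed in the sample size section.

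**The concern.** Asking for no more texts and leaving a trial are different decisions. The first concerns one channel of contact; the second ends outcome collection. The protocol ties them to a single word and offers no way to express only the first. Because the data rule speaks only of data gathered before withdrawal, a carer classed as withdrawn before month 12 has no primary outcome, even if that carer would have completed the 12-month survey from an email link.

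What is at stake is avoidable missing data on the primary endpoint. An analysis plan cannot repair this, because it cannot recover outcomes that were never collected.

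**Working it through.** **1. What the passages allow.**

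- Effect of 'stop': end of reminders and withdrawal. This is stated twice under Participant commitment (once per arm), once in the renegotiation answer, and three times in the site procedures: 2 + 1 + 3 = 6 places, all consistent.
- Reminder-only opt-out: not found anywhere.
- Link between 'stop' and the form: not stated. The protocol does not say that a 'stop' reply must be confirmed on the form, nor that the reply is enough by itself.
- Data after withdrawal: only earlier data are mentioned.

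Following the text literally, a 'stop' reply before the 12-month survey can cost that carer's primary outcome.

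**2. How many prompts.** Baseline data come before randomisation (Randomisation and interventions), so the baseline prompt cannot lose a randomised carer.

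- Lower end: 6 and 12 months only, 2 prompts. In the Arm 1 text the notification sentence follows the three outcome surveys and precedes any mention of the monthly survey. The site procedures tie the SMS to follow-up surveys. The cost-effectiveness section describes the monthly resource-use data as collected by interview.
- Upper end: 2 + 12 monthly surveys = 14 prompts. This rests on Arm 2 item (7), where the notification sentence comes after both kinds of survey.

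**3. What lost carers cost in power (illustration only).**

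Inputs from the sample size section: effect size 0.57, 66 per arm for 90% power, 92 per arm randomised, 40% attrition. Two-sided α = 0.05, from the analysis section.

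The plan's own figure first: a two-sample t-test with d = 0.57 and 90% power needs 65.66, so 66 per arm, which reproduces. The 92 per arm equals 66 × 1.4 = 92.4, rounded down. Dividing by the retained fraction would give 66 / 0.6 = 110 per arm. That is a separate matter, and the present point does not depend on it.

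Completers per arm: n = 92 × (1 − attrition). Normal approximation: power = Φ(0.57 × √(n/2) − 1.96). At 40% attrition: n = 55.2, 0.57 × √27.6 = 2.99, and Φ(1.03) = 0.850.

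| Attrition | n per arm | Power, normal | Power, t-test (n rounded down) |
|---|---|---|---|
| 35% | 59.8 | 87.6% | 86.7% |
| 40% | 55.2 | 85.0% | 84.2% |
| 45% | 50.6 | 81.8% | 80.6% |
| 50% | 46.0 | 78.0% | 77.2% |

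Successive 5-point steps cost 2.6, 3.2 and 3.8 points (normal) or 2.5, 3.6 and 3.4 points (t-test): about 3 to 4 points each. Only the 40% row is the protocol's assumption; the other rows are assumed, to show a range. No row is an estimate of what the 'stop' rule does.

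**The case against.** The strongest reply is that the rule is a consent safeguard. In the site procedures it sits beside the reminder that participants may leave at any stage, and an easy exit is a virtue. The 'stop' reply and the form are listed together in the renegotiation answer, so one can read the reply as signalling a wish that the form then records. The form and the information sheet are not shown and may offer graded choices. The section on managing time burden also lets a carer skip a component that takes too much time without leaving the study.

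Part of this stands. The protocol does not say what the researcher does after a 'stop' reply, so it is too strong to say that the form is bypassed or that follow-up certainly ends there. But permission to skip a component does not change the stated meaning of 'stop', and graded choices on a form do not help a carer whom the text already describes as withdrawing.

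A reader might infer several stronger things that the document does not support:

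- *The rule contradicts intention-to-treat.* The protocol uses the term for analysis by assigned group. It states no aim of measuring every randomised carer at 12 months, and data gathered before withdrawal remain usable in the repeated-measures model.
- *Most 'stop' replies would be mere message fatigue.* No frequency is given, and carers are reminded of their right to withdraw in the same process.
- *Loss would be unequal between arms.* The rule and the survey schedule are the same in both. The heavier total commitment in the intervention arm (27 against 9 hours at most) makes an imbalance conceivable, but does not show one.
- *The gap between 90% and about 84% power comes from this rule.* It comes from how 66 was inflated to 92. The assumed 40% may already include 'stop' replies.

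**Conclusion.** The point holds as a design weakness with a cheap remedy. The protocol gives one reply two meanings, provides no reminder-only choice, and does not reconcile the reply with its own withdrawal form. A carer who wants fewer texts can thereby be counted as withdrawn and lose the 12-month primary outcome, with 2 to 14 occasions for this after randomisation.

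The size of the loss cannot be estimated from the document. The exchange rate of about 3 to 4 points of power per 5 points of attrition assumes 92 randomised per arm, d = 0.57, a two-sided 5% test and a simple comparison of completers; it says what avoided losses would be worth, not how many there are. Bias is possible if those who reply 'stop' differ from those who stay, but neither its direction nor its size can be derived.

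**What to change.** In both arms' Participant commitment text, in the renegotiation answer and in the three site procedures, state that 'stop' ends SMS reminders only. Record withdrawal through the existing form or an explicit statement to the researcher, and say so in the section on the impact of withdrawal so that the two routes agree. Carers who stop the reminders are still invited to the 6- and 12-month surveys by email or post unless they decline follow-up. State also which surveys trigger an SMS.

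The change must apply only to messages sent after the amendment. Carers who replied 'stop' after being told that it meant withdrawal are treated as withdrawn and are not recontacted on the new basis.

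Cost: a small ethics amendment and revised SMS and information text. Withdrawal becomes slightly less immediate than a one-word reply, although an explicit statement to the researcher still suffices.

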**Participant follow up – how are participants monitored during the study?**

All carers in this study will undertake an online survey at three time points: baseline, 6 months and 12 months. The survey will enable researchers to monitor the effectiveness and cost-effectiveness of the education intervention for carers. Carers will also undertake a monthly 10-minute survey (online or hardcopy) to document the previous month health care services utilisation. Carers in the intervention group will also participate in monthly online carer group meeting for 12 months. The meetings will enable researchers to monitor how carers in the intervention group share their learning experience with peers and support each other.

**Consent**

Please refer to the National Statement 2.2 for guidance on consenting participants.

Where possible, informed consent should be sought from individuals to participate in research or to access their data for research purposes.

Consent can be provided in writing, implied (i.e. by return of a survey), opt in, opt out or verbally.

If consent cannot be obtained from the participant, a waiver of consent can be applied for which is reviewed and approved by the SAC HREC. The waiver of consent must be justified using the National Statement chapter 2.3.9 and 2.3.10 (a) to (i) in the HREA.

The investigator(s) should: - Determine, according to level of risk to participants, who of the study team is appropriate to lead the participant informed consent process. This should be documented on the “Delegation of Duties” log. (ICH GCP 5.7)

**How you will be obtaining consent and/or what alternatives you will be using:**

The researcher, [name] (or site-specific researchers to be hired) will explain the study to the potential carer participants and their care recipients; assess eligibility for inclusion based on cognitive assessment of the care recipients; assess the capacity of care recipients to take consent for MBS and PBS data used in the study; provide the PICF (simplified PICF for the care recipients) and MBS and PBS participant consent form, explain the forms to them and allow them sufficient time (at least 24 hours and a maximum of 3 days) to talk to their family and friends about their decision to participate in the study. Once the researcher has confirmed the carers and care recipients' decision to participate in the study, the researcher will sign written consent forms in one of the following methods: 1) post the hardcopy with pre-paid envelop; 2) meet them face to face 3) . Sign the electronic consent.

**Are you requesting a waiver of consent?**

☐ **Yes** – please justify why the waiver of consent is appropriate in the HREA

☒ **No**

**Which investigators will issue the information sheets and consent forms:**

In SALHN and Resthaven SA, the researcher, [name] who does not provide direct care to the person with dementia or their carers and has no relationship with the dementia care service providers, will issue the information sheets and consent forms to the participants.

In Bolton Clarke Victoria, CI [name] who is a Research Fellow at Bolton Clarke Research Institute does not provide direct care to the person with dementia or their carers and has no relationship with the dementia care service providers, will issue the information sheets and consent forms to the participants.

In Canberra Health Services, a site-specific researcher (to be hired) who does not provide direct care to the person with dementia or their carers and has no relationship with the dementia care service providers will issue the information sheets and consent forms to the participants.

**How much time will participants have to consider participation:**

At least 24 hours and maximum 7 days will be given to potential participants to consider participation. They are encouraged to discuss with their family, friends and colleagues regarding participation.

**Please specify which investigators will obtain consent from participants:**

In SALHN and Resthaven SA, researcher, [name] who does not provide direct care to the person with dementia or their carers and have no relationship with the dementia care service providers, will obtain consent after detailed explanation of the research project and assessment of eligibility for inclusion based on cognitive assessment.

In Bolton Clarke Victoria, CI [name] who is a Research Fellow at Bolton Clarke Research Institute does not provide direct care to the person with dementia or their carers and has no relationship with the dementia care service providers, will obtain consent after detailed explanation of the research project and assessment of eligibility for inclusion based on cognitive assessment.

In Canberra Health Services, a site-specific researcher (to be hired) who does not provide direct care to the person with dementia or their carers and have no relationship with the dementia care service providers, will obtain consent after detailed

explanation of the research project and assessment of eligibility for inclusion based on cognitive assessment.

**Will there be an opportunity to confirm or renegotiate consent during the research project?** – I.e. the capacity of the participant changes or the terms of consent / participation changes.

- (1) After the initial written consent, before each survey, a statement will be made to inform carer participants that by submitting the survey, they consent to participate in the study (implied consent).
- (2) Carers will be notified about each survey by email and an SMS message.. Carer can reply 'stop' to indicate the termination of the reminder and withdrawing from the study.
- (3) In the intervention group, program facilitator will gain verbal consent from participants to participate in each of carer support group meeting.
- (4) A withdraw consent form (Appendix H) will be used if participants wish to withdraw during the research when appropriate.

**Who will be confirming or renegotiating consent with participants and what process will be undertaken?**

**(1) SALHN and Resthaven SA sites:**

The researcher, [name] who obtained consent form from participants will be confirming or renegotiating consent with participants. She will send SMS to participants to remind them of each follow-up survey. She will also remind participants that they have the right to withdraw at any stage of the study. Participants can reply 'stop' to indicate the termination of the reminder and withdrawing from the study.

**(2) Bolton Clarke Victoria:**

CI [name] who obtained consent form from participants will be confirming or renegotiating consent with participants. The researcher will send SMS to participants to remind them of each follow-up survey. The researcher will also remind participants that they have the right to withdraw at any stage of the study. Participants can reply 'stop' to indicate the termination of the reminder and withdrawing from the study.

**(3) Canberra Health Services**

A site-specific researcher (to be hired) who obtained consent form from

participants will be confirming or renegotiating consent with participants. The researcher will send SMS to participants to remind them of each follow-up survey. The researcher will also remind participants that they have the right to withdraw at any stage of the study. Participants can reply 'stop' to indicate the termination of the reminder and withdrawing from the study.

**Conflicts of interest:** Please refer to the National Statement chapter 5.4, and your institutional policy for guidance.

☒ Yes / ☐ No

**Please provide details of the conflict of interest:**

Four team members are employed in a management role in participating organisations in the project. Therefore, they have potential conflict of interest. [name] is the Unit manager for Rehabilitation Ward, Southern Adelaide Local Health Network (SALHN) and [name] is the Regional Clinical Director for Rehabilitation and Aged Care, SALHN. Therefore, they have work relationships with people with dementia at SALHN. [name] is the Director, Palliative Care at Canberra Health Services and has work relationships with people with dementia at Canberra Health Services. [name] is the Executive Manager Community Services, Resthaven Incorporated at Resthaven SA. She has a leadership and management role in community aged care where participants will be recruited to the study.

**How will the conflict be managed?**

The potential conflict of interest will be managed by maintaining the confidentiality of all participants' data. These four members will not participate in the participant recruitment and data collection. Each participant in the study will be given a unique code. Only the PI, [name], and site-specific researchers employed to collect data will have the record of the participants' real name and code number. However, the four team members who have potential conflict of interest will be able to access de-identified data when participate in data analysis and in reporting findings.

## Ethical considerations

**Please describe the risk and burden associated with your research.** The National Statement chapter 2.1 provides guidance and advice on the definition of risk and how to gauge and manage it.

As an online psychoeducation intervention for carers of people with dementia and health

service research, we do not foresee any significant risks to any participants of this project. The foreseen risks are time burden on carers, especially those in the intervention group. Further, Carers may experience emotional, psychological distress from recalling experiences during the online survey or carer support group meetings. In addition, confidentiality of information may be breached that will threaten participants' privacy.

#### **How will any risks be managed?**

##### **Time burden:**

These risks will be managed by self-paced learning. Carers will choose the time and date that are suitable for them to engage in the online iSupport program. Participants also have the rights to choose the time that is convenient for them to participate in the online carer support group meetings. Any carer who feels the time commitment is too great to complete a given component of the study is under no compulsion to participate or may withdraw from the study at any point. Carers will receive \$50 per month for 12 months per person as a token of appreciation for their time contributing to the study.

##### **Emotional and psychological distress:**

In the online survey, participants will be instructed that they have the rights to choose whether they would like to answer some questions or not. In the carer support group meetings, the program facilitator will verbally instruct participants that they have the rights to choose whether they would like to answer some questions or not. They can leave the group discussion at any time if they do not feel comfortable in sharing their experiences. If they experience feelings of distress as a result of participation in this study, they are encouraged to let the research team know immediately. They will be offered counselling service or refer to relevant emergency service if required. They can also contact the following services for support:

Dementia Australia – [name]

Lifeline – [name], [www.lifeline.org.au](http://www.lifeline.org.au)

Beyond Blue – [name], [www.beyondblue.org.au](http://www.beyondblue.org.au)

##### **Potential breach of confidentiality of information**

Program facilitators will verbally remind carers in each carer group meeting to maintain confidentiality of information discussed in the group. The voice recorded meeting will be transcribed by [name] using NVivo Transcription software. Transcripts from group meetings and text messages will be de-identified by the researcher before the data analyses. Regarding the data received from MBS and PBS, the team will need to provide identifiable personal information to Services Australia to ensure data is extracted only for participants who have consented to the release of their data for this trial. However, this will be done via a password protected and encrypted file sent directly via registered post to Services

Australia, as per their requirements. The data from MBS and PBS will be sent back directly to the researcher conducting the analysis at Flinders University ([name]) and will be in de-identified format (i.e. all personal details removed). This information will be kept securely and separately from any data with identifying information containing identifying data to reduce the risk of any breaches in privacy and confidentiality.

**Benefits** – please identify and explain the expected outcomes and benefits of the study

This study aligns to the National priority areas in the Dementia, Ageing and Aged Care Mission Roadmap as it creates an innovative patient-centred care approach built on reciprocal partnerships between care service providers and carers that will reduce carers' stress and enable carers to manage dementia well at home and to prevent health conditions contributing to hospitalisations of PLWD. Therefore, these outcomes will improve health and QoL for PLWD and their carers and will ease the impact of dementia on the health care system. Further, the study will strengthen proactive health management by providing carers with psychoeducation which improves their ability to manage dementia and prevent changed behaviours and complications.

In addition, the 'Partnership in iSupport program' is an innovative patient-centred care model that targets the organisation's structures, resources and processes to improve care services. The program will be implemented by four industry partners in the project. Findings will provide evidence on the efficacy of an online education program in dementia care and in virtual social support that meet carers' needs. This program is designed to help carers seek practical solutions to their individual issues from the service provider and peers in a timely manner to prevent care crises that may trigger hospital admission, emergency department use and premature admission to residential aged care homes. The program is also designed to improve reach to carers in rural and remote areas and to carers of working age. The COVID-19 pandemic has highlighted the urgent need to have programs such as iSupport which are not impacted by lockdowns.

